#### Self-reported physical activity

In addition to the objective measures, self-reported physical activity will be measured by questions from the Danish National Health profile questionnaire [27] and a modified version of the question regarding spare-time physical activity used by Bengt Saltin and Gunnar Grimby [28].

#### Biochemical variables

Relevant plasma markers (HbA1c, HDL- and LDL-cholesterol, triglyceride) will be measured by means of a capillary test (DCA Vantage Analyzer, Siemens Healthcare, Siemens AG, Germany, Alere Cholestech LDX System, Alere Denmark).

#### Anthropometric and demographic variables

Arterial blood pressure will be measured in the sitting position (Omron M6 Blood pressure monitor, Omron Healthcare Europe B.V) after resting for at least five minutes. Three consecutive measurements will be obtained and the average of the last two measurements will be used. Body weight, waist circumference and height will be measured to the nearest 0.1 kg and 0.5 cm, respectively. Information regarding age, sex, ethnicity, current smoking status and medication will be obtained from the “Check your Health” database.

#### Health related quality of life

Health-related quality of life will be measured by the SF-12 [29].

Physical activity level and self-reported physical activity will be measured at baseline and 6 and 12 months. The rest of the secondary outcomes at baseline and 12 months.

### Data analysis

The primary analyses will be based on the *intention*-*to*-*treat* principle; however a per-protocol analysis will also be performed. Effect of the intervention on VO_2max_ will be estimated by the difference of the mean changes after 6 and 12 months between the intervention group and the comparison group. Furthermore a subgroup analysis regarding gender will be performed. A Student t-test or nonparametric test will be used for normally and unevenly distributed data, respectively. Loss to follow-up analyses will be conducted via baseline characteristics from Check your health and Danish Registers. Results will be presented with 95% confidence intervals (CI) and p values. P values of <0.05 will be considered as statistically significant.

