### Sample size

This study was calculated to detect a 3 ml/kg/minute (sd 6) difference between the intervention- and comparison group at the end of 6 months. The sample size calculation was based on unpuplished data from another randomised controlled health screening programme in Denmark showing a difference in cardiorespiratory fitness of 2,1 (sd 6) over a five year period and previous studies comparing 6 and 24 month intervention effects of a lifestyle physical activity program reporting differences between 3.64 (sd 3,5) and 1.34 (sd 3.37) ml/kg/minute respectively [19]. With a power of 90% using a two-sided p = 0.05 test, a sample size of at least 85 in each group will be necessary. To accommodate non-independence within couples, we used robust variance estimation to obtain valid uncertainty estimates and an extra 6 participants in each group will be added to the sample size. Anticipating a drop-out of 30%, a total of 118 participants will be included in each group.

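### The gender subgroup analysis names only two-group tests at p<0.05 and no test of whether the effect differs by gender; an arm-by-gender interaction contrast should decide that question (minor)

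*Protocol article*

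**What the plan says.** The Data analysis section defines the effect on VO2max as the between-group difference in mean change at 6 and 12 months. It then adds: "Furthermore a subgroup analysis regarding gender will be performed". The next sentence gives the test: "A Student t-test or nonparametric test will be used", with the choice depending on the distribution of the data. Results are to carry 95% confidence intervals and p values, and "P values of <0.05 will be considered as statistically significant". No other between-group test, no model and no rule for interpreting the subgroup is given.

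The Sample size section covers the whole sample only. The trial was "calculated to detect a 3 ml/kg/minute (sd 6) difference between the intervention- and comparison group", and "With a power of 90% using a two-sided p = 0.05 test, a sample size of at least 85 in each group will be necessary". For couples, "an extra 6 participants in each group will be added to the sample size", and the section mentions robust variance estimation to deal with dependence within couples. Finally, "Anticipating a drop-out of 30%, a total of 118 participants will be included in each group". The expected split between men and women is not stated.

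**The concern.** A t-test or rank test compares two groups. Used for a gender subgroup, it gives one arm comparison in men and another in women. Neither p value, nor the pair, answers the question a subgroup analysis raises, which is whether the effect is different in men and women. Each sex also supplies only part of a sample that was sized for the overall comparison, so one significant and one non-significant result is a likely outcome even when the true effect is the same in both.

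What is at stake is a spurious statement that the programme works in one sex only. The Discussion section wants readers to be able to judge how far the results apply in their own setting, and such a statement would mislead them. The overall comparison is not touched.

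**Working it through.** **Inputs from the Sample size section.** Difference 3 ml/kg/min, SD 6, two-sided 0.05, power 90%, 85 per arm before allowances, 118 randomised per arm, 30% drop-out.

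**Assumptions, because the article gives no figure.** Sex split from 50:50 to 80:20, the same in both arms; one common effect and SD in both sexes; the men's and women's estimates independent.

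**Step 1, the plan's own figure.** n per arm = 2 × (1.96 + 1.2816)² × 6² / 3² = 84.06, rounded up to 85. The stated figure is reproduced; noncentral-t power at 85 per arm is 90.0%.

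**Step 2, analysed numbers.** 118 × 0.70 = 82.6, so about 83 per arm. Both 83 and 85 are used below.

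**Step 3, power within each sex and discordance.** Power p1 and p2 comes from the noncentral t distribution with n per arm in that sex. The chance that exactly one sex is significant is p1(1 − p2) + p2(1 − p1).

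| Analysed per arm | Split (n per arm in each sex) | p1 | p2 | Exactly one significant |
|---|---|---|---|---|
| 85 | 50:50 (42 / 43) | 0.620 | 0.630 | 0.469 |
| 85 | 60:40 (51 / 34) | 0.706 | 0.529 | 0.488 |
| 85 | 70:30 (59 / 26) | 0.768 | 0.424 | 0.541 |
| 85 | 80:20 (68 / 17) | 0.825 | 0.293 | 0.635 |
| 83 | 50:50 (42 / 41) | 0.620 | 0.609 | 0.474 |
| 83 | 80:20 (66 / 17) | 0.814 | 0.293 | 0.630 |

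For the first row: 0.620 × 0.370 + 0.630 × 0.380 = 0.469. With no drop-out at all (118 per arm) the range is 0.356 to 0.589.

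**Step 4, the interaction test under the same common effect.** In 200,000 simulated trials it declared a gender difference in 5.0%, both with 43 / 42 and with 60 / 25 per arm. Among simulated trials with a significant overall result, exactly one sex was significant in 49% and 58% respectively.

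**Step 5, what the interaction can detect.** SE = 6 × √(2/n1 + 2/n2). At 42 / 43 this is 1.84, and 1.84 × (1.96 + 0.8416) = 5.16 ml/kg/min for 80% power; at 42 / 41 it is 5.22. At 68 / 17 it is 2.30 × 2.8016 = 6.45. A gender difference in effect of 3 ml/kg/min would be found with 37% power at 50:50 and 26% at 80:20.

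**Step 6, sensitivity to effect and SD.** The article also cites a lifestyle programme "reporting differences between 3.64 (sd 3,5) and 1.34 (sd 3.37) ml/kg/minute respectively". With 85 per arm, the chance that exactly one sex is significant is:

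| Effect, SD | 43 / 42 | 60 / 25 | 68 / 17 |
|---|---|---|---|
| 3, 6 | 0.469 | 0.549 | 0.635 |
| 1.34, 3.37 | 0.493 | 0.535 | 0.580 |
| 3, 3.5 | 0.050 | 0.159 | 0.322 |
| 3.64, 3.5 | 0.005 | 0.050 | 0.164 |

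So with SD 3.5 and effects of 3 to 3.64 the rate is about 0.5 to 16% for splits from even to about 70:30 (60/85 = 71%). It is higher if the split is as uneven as 80:20.

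**The case against.** The strongest objection is that the fault is read out of silence. The subgroup sentence states no method. The test sentence is a general rule about data distribution and is not tied to the subgroup. This is a condensed article, and the way a subgroup is tested is often left to a full protocol or SAP that is not shown. Much of this stands. A reader might infer that the plan excludes an interaction test, or that it commits the authors to claiming an effect in one sex only. The documents support neither: no interaction test is ruled out, no rule for one-sex claims is given, and confidence intervals are promised alongside p values. The point must therefore be conditional. It is still more than a missing detail, because the article does name its between-group tests and its threshold, and these cannot answer the subgroup question.

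A reader might also infer that dependence within couples is ignored. That goes too far, since the Sample size section mentions robust variance estimation. The Data analysis section does not say how this combines with a t-test or rank test.

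Two objections to the size also stand. The figure of about half depends on SD 6; Step 6 shows much lower rates with SD 3.5 and effects of 3 to 3.64. The discordance formula treats the sexes as independent, whereas couples are allocated together, so positive correlation within mixed-sex couples would lower the rate somewhat. Against this, SD 6 is the plan's own planning value, and the smaller of the two cited effects (1.34, SD 3.37) again gives about half.

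**Conclusion.** The point holds in conditional form and is minor. The article plans a gender subgroup analysis and names only two-group tests at p<0.05, with no test of a difference between the sexes. If those tests are run within each sex, a common effect of 3 ml/kg/min with SD 6 and about 83 to 85 analysed per arm would be significant in exactly one sex in about 47% (50:50 split) to 63% (80:20) of trials, against 5% for an interaction test. This rests on an assumed sex split, independence between the sexes and the planning SD. The subgroup analysis can only be exploratory, because even with an even split the effects would have to differ by about 5.2 ml/kg/min, more than the planned effect itself, to be detected with 80% power. The primary conclusion is unaffected.

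**What to change.** State in the analysis section or the SAP that any gender difference will be judged by an arm-by-gender interaction contrast on change in VO2max, with the couple-robust standard errors that the Sample size section already mentions. Report the effect in men, the effect in women and the difference between them, each with a 95% CI. Label the analysis exploratory, and say that within-sex p values will not be used to claim that the effect is confined to one sex. The contrast can be fitted to the change scores the article already specifies, so no new primary model is needed.

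The cost is a sentence or two and no extra data. The trade-off is that sex-specific significance claims are given up, and that the interaction test itself has little power. That is why the estimates and intervals should carry the message, and why a non-significant interaction should not be read as proof of equal effects.

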## Methods

### Study design

The study is conducted as a single (researcher) blinded randomised controlled trial higly explanatory in attitude delivered under as optimal conditions as possible [18]. The randomisation sequence will be computer-generated by an independent statistician. Block randomisation will be applied to ensure that couples living together will be randomised to the same group. The allocation to either comparison or intervention group will take place at the front desk at Randers Health Care Centre, and an e-mail will subsequently be sent to either the person in charge of the comparison group or the person in charge of the intervention group (project secretary). See Figure 1 for a flow diagramme of the study.

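### Couples share an arm and the sample-size section calls for robust variance, but the analysis section names only tests that assume independent participants; followed as written, CIs and p values are modestly too optimistic

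*Protocol article*

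**What the plan says.** Three sections of the protocol article bear on this point.

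- **Study design** makes the couple the unit of allocation: "Block randomisation will be applied to ensure that couples living together will be randomised to the same group".
- **Sample size** accepts the consequence. After a base calculation of 85 per group it says "To accommodate non-independence within couples, we used robust variance estimation to obtain valid uncertainty estimates", and continues that "an extra 6 participants in each group will be added to the sample size".
- **Data analysis** defines the effect on VO2max as a quantity that "will be estimated by the difference of the mean changes after 6 and 12 months between the intervention group and the comparison group", and then names the tests: "A Student t-test or nonparametric test will be used for normally and unevenly distributed data, respectively". It commits to 95% CIs, p values and a 0.05 threshold. It mentions no robust variance, couple term or couple-level test.

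**The concern.** Partners allocated together are a cluster of two inside one arm. If their changes in fitness are positively correlated, the two of them carry less information than two unrelated participants, and the variance of the difference between arms is larger than the independence formula says. The Student t-test and the usual rank tests both rely on independence, so moving to the nonparametric option does not remove the problem.

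The issue is not missing detail. The analysis section fixes a test, and that test does not use the variance method which the sample-size section says is needed for valid uncertainty estimates. At stake are the CI and p value for the primary outcome. Two incompatible methods on record also leave room to choose between them after the data are seen, which matters most when a result lies near 0.05.

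**Working it through.** **Inputs from the protocol article**
- Difference 3 ml/kg/min, SD 6, at 6 months (Sample size).
- Two-sided 0.05, power 90%, 85 per group (Sample size).
- Couple allowance of 6 per group (Sample size).
- Couples in the same arm (Study design).

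**Inputs not in the document, therefore assumptions**
- f, the share of participants enrolled together with their partner.
- ρ, the within-couple correlation (ICC) of the change in VO2max.

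**1. Reproduce the base sample size.**
n per group = 2 × [SD × (z₀.₉₇₅ + z₀.₉₀) / difference]² = 2 × [6 × (1.960 + 1.282) / 3]² = 84.06, rounded up to 85. This matches the stated figure.

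**2. Design effect implied by the allowance.**
(85 + 6) / 85 = 91/85 = 1.071.

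**3. How couples enter the variance.**
In an arm of n participants there are nf/2 couples. The variance of the arm total is nσ² + 2 × (nf/2) × ρσ² = nσ²(1 + fρ), so the design effect is DE = 1 + fρ. The ordinary t-test omits the factor DE. Hence:
- correct SE / reported SE = √DE
- true type I error = 2 × [1 − Φ(1.960/√DE)]
- true coverage of the nominal 95% CI = 1 minus that value

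**4. At the protocol's own allowance (DE = 1.071).**
- √1.071 = 1.035, so the correct SE is about 3.5% larger.
- 1.960/1.035 = 1.894, so type I error is about 0.058 and coverage about 94.2%.
- With 91 analysed per group and SD 6, the unadjusted CI half-width is 1.960 × 6 × √(2/91) = 1.74 ml/kg/min. The adjusted one is 1.74 × 1.035 = 1.80.

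**5. Range under assumed f and ρ.**

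| f | ρ | DE | Type I error |
|---|---|---|---|
| 0.10 | 0.3 | 1.03 | 0.0535 |
| 0.20 | 0.3 | 1.06 | 0.057 |
| 0.20 | 0.5 | 1.10 | 0.062 |
| 0.30 | 0.5 | 1.15 | 0.068 |
| 0.50 | 0.5 | 1.25 | 0.080 |

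The protocol's 1.071 corresponds, for instance, to f of about 0.14 with ρ = 0.5 (0.071/0.5 = 0.14).

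**6. Simulation check, 91 per arm, no true difference.**

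| f | ρ | t-test | Mann-Whitney |
|---|---|---|---|
| 0 | – | 0.049 | 0.048 |
| 0.14 | 0.5 | 0.057 | 0.057 |
| 0.20 | 0.3 | 0.057 | 0.057 |
| 0.30 | 0.5 | 0.070 | 0.069 |

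The simulation agrees with the formula, and the rank test behaves like the t-test.

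**The case against.** The best defence is that the robust-variance sentence is already a statement about the analysis. Uncertainty estimates come from outcome data, not from a sample-size formula, so the authors may intend robust standard errors and have placed the sentence in the wrong section. This is also a condensed article without its statistical analysis plan, and the choice of variance estimator is often left to that plan. Both points are fair. They rule out the inference that the final analysis will certainly ignore couples. They do not remove the conflict: the only analysis section names a different method, and a reader following it would not adjust.

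The defence can also fairly say that the problem is small. Both partners must be aged 30–49, fall below the fitness cut-offs, pass the exclusion criteria and volunteer, so the couple share may well be low. This stands, and it limits two stronger readings that a reader might be tempted by:

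- **That a type I error of 7–8% is to be expected.** Such figures need about a third to a half of participants enrolled as couples with an ICC of 0.5. The document gives neither value, and its own allowance implies much less.
- **That every secondary outcome under-covers.** This requires a positive within-couple correlation in each outcome. The document gives none, and shared exercise habits do not by themselves establish one for HbA1c, lipids or SF-12.

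**Conclusion.** The conflict is real and lies within the document: same-arm couples and a stated need for robust variance on one side, named tests that assume independence on the other. If Data analysis is followed as written, the CI and p value for the primary outcome are modestly too optimistic. The only size that rests on the document's own figures is a type I error of about 5.8%, with coverage of about 94.2% and an SE that should be about 3.5% larger. Under assumed couple shares of 10% to 50% and ICCs of 0.3 to 0.5, the type I error runs from about 5.35% to about 8%.

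The direction depends on a positive within-couple correlation, which the protocol presupposes by adding participants for it. The conclusion also depends on the analysis section meaning what it says. If robust variance was intended all along, the defect is that this section fails to say so, and the correction is the same.

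**What to change.** Amend the Data analysis section to say, in substance:

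- Between-group differences in mean change will be estimated by linear regression with standard errors clustered on couple, participants enrolled without a partner counting as clusters of one.
- Where a nonparametric method is used for non-normal outcomes, it will also respect couples, for example a permutation test that reassigns whole couples and singletons between arms.

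The second sentence is needed because replacing the t-test alone would either leave the rank test uncorrected or silently drop the nonparametric route.

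The cost is small. The couple identifier must already exist for allocation, so no new data are needed, and the 6 extra participants per group were added for this purpose. CIs widen slightly, by about 3.5% on the protocol's own allowance.

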**Methods/Design:**

Two-armed randomised controlled trial with 6 and 12 months follow-up. The primary outcome is cardiorespiratory fitness estimated via a maximal incremental exercise test. Secondary outcomes include physical activity level and sedentary behavior (objectively measured), self-reported physical activity, biochemical parameters (HbA_1C_, HDL- and LDL-cholesterol, and triglyceride), anthropometric parameters and health-related quality of life. A total of 236 participants with low levels of cardiorespiratory fitness classified at a local health check programme will be randomised. The intervention consists of four motivational interviews, a six months membership to a sport club, and a global positioning watch to upload training activity to Endomondo.com. The comparison group will receive standard care: a one hour motivational interview followed by another interview if requested. Effects will be estimated by evaluating the differences in mean changes in cardiorespiratory fitness between the two groups.

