#### Virtual software platform

The participants will be required to upload training activities and pulse data at least once a week to the virtual software platform Endomondo.com via a global positioning system (GPS)-watch (Garmin Forerunner 210). Endomondo.com is an online sports community based on free real-time GPS-tracking of running, cycling, cross-training etc. At this site, it is possible to get a complete training log, to measure training progression and compare data with other study participants or friends. It is also possible to key in activities that are unmeasurable via the GPS-watch eg. water activities. The participants will get to keep the watch if they attend the 12-month follow-up.

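### The analysis labelled intention-to-treat uses a test on change scores that, as written, can include only participants with a follow-up VO2max; at 12 months an attendance reward stated for one arm adds a risk of differential attrition

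*Protocol article*

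**What the plan says.** All references are to the protocol article.

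- **Data analysis**, on principle: "The primary analyses will be based on the *intention*-*to*-*treat* principle; however a per-protocol analysis will also be performed".
- **Data analysis**, on the effect measure: the "difference of the mean changes after 6 and 12 months between the intervention group and the comparison group".
- **Data analysis**, on the test: "A Student t-test or nonparametric test will be used for normally and unevenly distributed data, respectively".
- **Data analysis**, on loss to follow-up: "Loss to follow-up analyses will be conducted via baseline characteristics from Check your health and Danish Registers". The section names no other provision for missing outcomes.
- **Sample size**: "Anticipating a drop-out of 30%, a total of 118 participants will be included in each group". The target is 3 ml/kg/min (SD 6) at 6 months. The section also promises robust variance estimation for couples.
- **Primary outcome**: VO2max is measured at baseline, 6 months and 12 months.
- **Virtual software platform**, under the intervention group: "The participants will get to keep the watch if they attend the 12-month follow-up". The abstract lists the watch as part of the intervention package: "The intervention consists of four motivational interviews, a six months membership to a sport club, and a global positioning watch".
- **Comparison group**: one motivational interview and a second on request. No watch or other attendance reward is stated.

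**The concern.** Intention-to-treat means that participants are compared as randomised. A change in VO2max can be calculated only for someone tested both at baseline and at the follow-up visit. Unless something is done about missing values, a t-test on changes is therefore a comparison of completers. Comparing the baseline characteristics of those lost and those retained shows whether the two differ, but does not carry that information into the effect estimate.

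The completers' difference is biased if loss is related to how fitness would have changed and either the share lost or that relation differs between arms. The protocol gives a specific reason to expect unequal attendance at 12 months: one arm is offered a watch to keep for attending, and nothing similar is stated for the other.

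The test also wastes information. A participant tested at 6 but not at 12 months contributes nothing to the 12-month comparison, although the 6-month value says something about the missing one.

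**Working it through.** **1. The plan's own figure.** Inputs from Sample size: difference 3, SD 6, two-sided 0.05, power 90%.

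n per arm = 2 × [6 × (1.960 + 1.282) / 3]² = 84.06, rounded up to 85. This reproduces the stated 85. Adding 6 for couples gives 91. The stated 118 corresponds to 91 × 1.3 = 118.3. (Dividing by 0.7 would give 130; that is a separate matter and not part of this point.)

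**2. Who has a change score.** With 30% loss, 118 × 0.7 = 82.6 per arm, or 236 × 0.7 = 165.2 in total. About 236 × 0.3 = 70.8, i.e. 71 randomised participants, have no change score. The article does not say to which visit the 30% applies.

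**3. Cost in power.** With 82.6 per arm the standard error is 6 × √(2/82.6) = 0.93, and power at a true difference of 3 is 89.5%. If the couples allowance is used as a design effect (91/85), the effective number is 82.6 × 85/91 = 77.2 and power is 87.4%. Power is little affected, so the main issue is possible bias.

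**4. Form of the bias.** In one arm, let d be the share lost and g the mean change in those retained minus that in those lost. The mean over all randomised is (1 − d) × retained mean + d × lost mean, so the retained mean exceeds it by d × g. The completers' difference is therefore off by

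bias = d(I) × g(I) − d(C) × g(C),

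with I for intervention and C for comparison.

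**5. Illustration.** The documents give neither d by arm nor g. The values below are assumptions, with overall loss held at 30% and the same g in both arms.

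| Loss, I vs C | g = 1 | g = 2 | g = 3 |
|---|---|---|---|
| 30% vs 30% | 0 | 0 | 0 |
| 25% vs 35% | −0.1 | −0.2 | −0.3 |
| 20% vs 40% | −0.2 | −0.4 | −0.6 |

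In ml/kg/min, the non-zero shifts are 0.1/3 = 3% to 0.6/3 = 20% of the target. Negative values understate the intervention effect. If the intervention arm loses more, the signs reverse.

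Equal loss does not guarantee safety. With 30% lost in both arms and g differing between arms by 1 to 3, the shift is 0.3 × 1 = 0.3 to 0.3 × 3 = 0.9, in either direction.

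**6. Which visit the watch affects.** The reward is tied to the 12-month visit and the sample size to 6 months. The incentive therefore bears on the 12-month comparison. The restriction to participants with a follow-up test applies at both visits.

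**The case against.** The strongest reply is that the article never says drop-outs are excluded. It names a contrast and a test, and imputed changes can also be compared by t-test. The section is visibly condensed: it does not even repeat the couple-robust variance promised under Sample size. A statistical analysis plan that is not shown may hold the missing-data rules, and the article's silence on them is not an error. Attrition was plainly anticipated, in the sample size and in the planned loss-to-follow-up analyses.

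Much of this stands. Exclusion is inferred from the named test and is not a stated rule, and the lack of an imputation method is not the point here. What remains is what the article does fix: an intention-to-treat label attached to a test that, as described, cannot deliver it and does not give the promised couple-robust variance.

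Three stronger readings are tempting, and the documents do not support them:

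- *The watch biases the powered comparison.* The reward depends on the 12-month visit, and the trial is powered at 6 months. Participants seen at 6 months count there whether or not they return.
- *The result will be biased by a known amount or in a known direction.* The split between arms and the gap are both assumed. In the tabulated case the shift is towards no effect, so it would not create a false positive; other patterns would overstate the effect.
- *The comparison arm certainly gets no reward.* The article states none, which in a condensed text is not proof that there is none.

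It is also fair to say that a mixed model is no cure. It assumes that data are missing at random, and someone lost before 6 months contributes only a baseline value.

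**Conclusion.** The point holds as a mismatch between stated principle and stated method. At the anticipated 30% loss, the named test can use about 165 of 236 randomised participants, and the planned description of drop-outs does not change the estimate. At 12 months the attendance reward stated for one arm makes unequal loss foreseeable.

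The cost in power is small. The bias cannot be derived from the documents: the 0.1 to 0.6 ml/kg/min illustration rests on assumed loss splits, an assumed completer-minus-drop-out gap of 1 to 3, and the same gap in both arms. Its sign depends on which arm loses more. The case for change is that a better method is available from data already planned, not that a particular bias has been shown.

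**What to change.** - Replace the t-test on changes with one repeated-measures mixed model of baseline, 6- and 12-month VO2max, with arm-by-time effects, baseline constrained equal between arms and standard errors robust to clustering within couples. Include every randomised participant with any measurement. Report the arm differences at 6 and 12 months from this model.
- Use the predictors of drop-out from Check your health and the registers in a sensitivity analysis for missing outcomes, and not only to describe those lost.
- Report attrition by arm at each visit, and note the arm-specific watch incentive as a limitation of the 12-month comparison.
- If an analysis plan already specifies such methods, align the published description with it.

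No new data are needed. The cost is a little more analysis work and reliance on missing-at-random in the main model, which the sensitivity analysis is there to probe. The gain is that 6-month data from those lost before 12 months are used, baseline is adjusted for, and the promised couple-robust variance is delivered.

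### The trial is sized for VO2max at 6 months, but the primary outcome is analysed at 6 and 12 months with neither named as primary, so error on the primary claim can exceed 5%

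*Protocol article*

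**What the plan says.** VO2max is the only primary outcome in the protocol article. The Sample size section ties it to one visit: the study was "calculated to detect a 3 ml/kg/minute (sd 6) difference between the intervention- and comparison group at the end of 6 months".

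The Primary outcome section schedules the measurement at baseline, 6 months and 12 months and singles out neither follow-up. The Data analysis section says that the effect on VO2max will be "estimated by the difference of the mean changes after 6 and 12 months", comparing the two arms. It closes with one criterion for all results: "P values of <0.05 will be considered as statistically significant". The Abstract also lists both follow-ups side by side.

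No section names a primary time point, orders the two tests, divides the 5% between them, or says whether one or both must be significant.

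**The concern.** The sample size section and the analysis section describe different primary tests. The first has one comparison, at 6 months. The second has two comparisons of the same outcome, each open to the 0.05 criterion.

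The two visits answer different questions. The intervention package lasts six months, so the 6-month visit measures the effect at the end of the intervention and the 12-month visit measures whether it persists. The two results may well differ: the earlier lifestyle programme cited in the Sample size section showed a difference of 3.64 ml/kg/min at 6 months and 1.34 at 24 months.

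If one visit is significant and the other is not, the text does not settle which result is the primary one. A trial that misses at 6 months could report a positive 12-month comparison as its main finding, and the nominal 5% would then not describe that claim.

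**Working it through.** **Inputs from the article.** Difference 3 ml/kg/min, SD 6, two-sided 0.05, power 90%, time point 6 months (Sample size); two follow-up comparisons of VO2max (Primary outcome, Data analysis); threshold 0.05 (Data analysis).

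**Input not in the article.** The correlation r between the 6-month and 12-month test statistics. It is varied below.

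**Step 1: reproduce the plan's own figure.** The article states: "With a power of 90% using a two-sided p = 0.05 test, a sample size of at least 85 in each group will be necessary".

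n per arm = 2 × (1.960 + 1.282)² × 6² / 3² = 2 × 10.51 × 4 = 84.1, rounded up to 85.

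Power at 85 per arm is 90.3% by the normal approximation and 90.0% by the t-test. The figure reproduces, and it belongs to one test at one visit at the full 0.05.

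**Step 2: error if either visit may be claimed.** With no true effect at either visit,

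P(at least one false positive) = 1 − P(|Z6| ≤ 1.96 and |Z12| ≤ 1.96),

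where Z6 and Z12 are bivariate normal with correlation r. At r = 0 this is 1 − 0.95² = 0.0975, the largest value it can take. For other values of r:

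| r (assumed) | Chance of at least one false positive |
|---|---|
| 0 | 9.75% |
| 0.5 | 9.1% |
| 0.6 | 8.75% |
| 0.7 | 8.35% |
| 0.8 | 7.8% |
| 0.9 | 7.0% |
| 0.95 | 6.5% |

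A value of 0.5 is a natural reference. Take equal variances σ² at the three visits and the same correlation ρ between any two of them. The two change scores share the baseline, so their covariance is (1 − ρ)σ² and each has variance 2(1 − ρ)σ². Their ratio is 0.5.

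**Step 3: error under other decision rules.**

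- 6 months is the single primary test: 5%.
- 6 months first, and 12 months only if 6 months is significant: at most 5%.
- Both visits must be significant: at most 5%.
- Either visit, each tested at 0.025: at most 4.9% (1 − 0.975² = 0.0494).

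**The case against.** The strongest reply is that the article already points to 6 months. The trial was sized on that visit, and the package and the club membership last six months, so 12 months reads naturally as follow-up after the intervention. On that reading the primary test has 5% error. The 0.05 sentence is also a general convention, and nowhere does the article say that a 12-month result alone would count as success.

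This stands in part. A reader might infer that the false-positive chance simply is 8% to 9% rather than 5%. The article does not support that as a flat statement, because it needs both a rule that either visit suffices and a correlation that the article does not give. But the 6-month reading is itself an inference. The section that defines the analysis lists both visits on the same footing.

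A second reply is that a journal article leaves testing order and alpha allocation to the full protocol or the SAP. That is fair for the detail of a multiplicity scheme. It does not cover a mismatch between two sections of the same article over which visit carries the primary outcome.

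Two further readings are tempting and should not be pressed:

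- A reader might infer that the gender analysis is a t-test within each sex. The article says only: "Furthermore a subgroup analysis regarding gender will be performed". The sentence on t-tests and nonparametric tests that follows is general, and an interaction test is not excluded.
- A reader might infer that the per-protocol analysis competes with the main one. The Data analysis section already bases the primary analyses on intention to treat and adds the per-protocol analysis alongside.

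**Conclusion.** The mismatch is real: the sample size covers VO2max at 6 months, while the analysis covers 6 and 12 months without ranking them. The inflation of error is conditional. If a significant result at either visit may be claimed as primary, the false-positive chance is above 5% and at most 9.75%. It is about 9.1% to 7.8% for an assumed correlation of 0.5 to 0.8, and 6.5% at 0.95. If 6 months is meant as the only primary test, the error is 5% and all that is missing is the sentence saying so. The case for the change does not depend on the exact percentage, because under any correlation the text leaves open which result is the primary one.

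**What to change.** In the Data analysis section, state that the difference between arms in mean VO2max change at 6 months, by intention to treat, is the single primary test at two-sided 0.05, as in the sample size calculation. State that the 12-month difference is secondary, or that it is tested second in a fixed sequence and only if the 6-month test is significant. Either wording settles the matter.

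The cost is one or two sentences and the loss of a stand-alone primary claim at 12 months. The calculated 85 per arm does not change. Keeping both visits as co-equal routes to success would cost more. With each tested at 0.025, 90% power needs 2 × (2.241 + 1.282)² × 4 = 99.3, so 100 per arm; at 85 per arm power falls to 84.6%.
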